## Part A (MRA)

17. Contraindication to terlipressin acetate.

18. Body mass index (BMI) ( $\text{weight}[\text{kg}] / \text{height}[\text{m}]^2$ ) > 40 kg/m^2.

19. Any contraindication to having an MRI scan including:

- Brain aneurysm clip
- Implanted neural stimulator
- Implanted cardiac pacemaker, pacemaker wires or defibrillator
- Prosthetic heart valves
- Cochlear implant
- Ocular foreign body (e.g. metal shavings)
- Other implanted medical devices (e.g. Swan Ganz catheter)
- Implanted insulin pump
- Metal shrapnel or bullet
- Severe claustrophobia
- Tattoos (at the discretion of the local imager)
- Any additional contraindications to MRI at the local facility that will perform the test

## **Part B (direct venous pressure measurement)**

20. Contraindication to catheterization (e.g. portal vein thrombosis, overt hepatic encephalopathy, severe cardiac or pulmonary disease).

## **5 Treatment**

### **5.1 Investigational and control treatment**

The sponsor will provide the following open label bulk medication for Part A:

- Glypressin® commercial pack, each ampoule contains 1mg of terlipressin acetate in 8.5mL solution for injection
- Serelaxin (RLX030) solution 3.5mg/ 3.5mL per vial (1.0mg/mL)

The sponsor will provide the following open label study medication for Part B:

- Serelaxin (RLX030) solution 3.5mg/3.5mL per vial (1.0mg/mL)

### **5.2 Treatment arms**

#### **Part A (MRA)**

40 patients will be assigned to one of the following two treatment arms in a ratio of 1:1:

- Terlipressin (2mg i.v. bolus)
- Serelaxin (RLX030) (i.v. infusion: 80 µg/kg/d for 60 min followed by 30 µg/kg/d for at least 60 min)

#### **Part B (direct venous pressure measurement)**

6 patients will be enrolled into the following treatment arm:

- Serelaxin (RLX030) (i.v. infusion: 80 µg/kg/d for 60 min followed by 30 µg/kg/d for at least 60 min)

### **5.3 Treatment assignment**

For part A only, treatment allocation cards will be utilized for treatment group assignment (part B will not require the use of such cards). One set of treatment allocation cards with unique randomization numbers printed on them and covered by a removable, scratch-off covering will be provided for use at the clinical site.

The investigator or his/her delegate will scratch-off the covering of the treatment allocation card with the lowest available, unassigned randomization number thus revealing the treatment group the patient is assigned to after confirming that the patient fulfills all the inclusion/exclusion criteria for part A.

The patient randomization list will be produced by Novartis Drug Supply Management using a validated system that automates the random assignment of randomization numbers to the two different treatment groups. These randomization numbers are linked to the different treatment arms.

The randomization scheme for patients will be reviewed and approved by a member of the Biostatistics Quality Assurance Group.

## **5.4 Treatment blinding**

Open label supplies will be used as this is an open label study. Treatment allocation cards will be provided to reveal the treatment each patient has been randomly assigned to receive.

## **5.5 Treating the patient**

### **5.5.1 Patient numbering**

Each patient is uniquely identified in the study by a combination of his/her center number and patient number. The center number is assigned by Novartis to the investigative site. Upon signing the informed consent form, the patient is assigned a patient number by the investigator. At each site, the first patient is assigned patient number 1, and subsequent patients are assigned consecutive numbers (e.g. the second patient is assigned patient number 2, the third patient is assigned patient number 3). Once assigned to a patient, a patient number will not be reused. If the patient fails to be randomized/assigned to treatment for any reason, the reason for not being randomized/assigned to treatment will be entered on the Screening Log, and the Demography eCRF should also be completed.

Re-screening of patients who failed screening is not allowed.

### **5.5.2 Dispensing the study treatment**

Each study site will be supplied by Novartis with open-label bulk Serelaxin study drug for study part A2 and B. No unique medication numbers will be used. The primary and secondary packaging will have simple labels only.

Commercial Glypressin® product will be purchased and provided by Novartis and used for study part A1. Simple labels will be affixed to fulfil study drug labelling requirements.

Bulk medication labels will be in local language, will comply with the legal requirements of the country and will include storage conditions for the drug but not information about the subject.

Investigator staff will select the study drug according to the patient's treatment assignment and document this in the source documents. The randomization number must also be recorded on the Randomization Number eCRF (part A only).

### **5.5.3 Supply, storage and tracking of study treatment**

Study treatment must be received by a designated person at the study site, handled and stored safely and properly, and kept in a secured location to which only the investigator and designated assistants have access. Upon receipt, all study drugs should be stored according to the instructions specified on the drug labels. Clinical supplies are to be dispensed only in accordance with the protocol.

Medication labels will be in the local language and comply with the legal requirements of each country. They will include storage conditions for the drug, but no information about the patient.

The investigator must maintain an accurate record of the shipment and dispensing of study drug in a drug accountability ledger. Monitoring of drug accountability will be performed by the field monitor during site visits and at the completion of the trial. Patients will be asked to return all unused study drug and packaging at the end of the study or at the time of study drug discontinuation.

At the conclusion of the study, and as appropriate during the course of the study, the investigator will return all used and unused study drug, packaging, drug labels, and a copy of the completed drug accountability ledger to the Novartis monitor or to the Novartis address provided in the investigator folder at each site.

#### **5.5.4 Instructions for administering study treatment**

**For Part A1:** Terlipressin acetate will be administered via slow i.v. bolus injection of 2mg (over 3-5 min) just after completion of the first MRA assessment at visit 2.

**For Part A2:** Serelaxin will be administered via i.v. infusion at two different infusion rates: 80 µg/kg/day for 60 minutes followed by 30 µg/kg/day for at least 60 minutes (until completion of the second MRA assessment and the other 120 min assessments at visit 2).

**For Part B:** Serelaxin will be administered via i.v. infusion at two different infusion rates: 80 µg/kg/day for 60 minutes followed by 30 µg/kg/day for at least 60 minutes (until completion of the second inferior vena cava pressure (IVCP) measurement and the other 120 min assessments at visit 2).

For detailed instructions on preparation and administration of study drug, please refer to the pharmacy manual that will be provided separately.

All dosages administered to the patient and all dose changes during the study must be recorded on the Dosage Administration Record eCRF.

#### **5.5.5 Permitted dose adjustments and interruptions of study treatment**

Dose adjustments and/or interruptions of study treatment are not permitted.

Any study drug adjustment and/or interruption must be recorded on the Dosage Administration Record eCRF.

#### **5.5.6 Rescue medication**

Rescue medication to treat severe or serious condition in the opinion of the investigator is allowed. Use of rescue medication must be recorded on the Concomitant medications/Significant non-drug therapies after start of study drug eCRF.

#### **5.5.7 Concomitant treatment**

The investigator should instruct the patient to notify the study site about any new medications he/she takes after the start of the study drug. All medications and significant non-drug therapies (including physical therapy and blood transfusions) administered after the patient starts treatment with study drug must be listed on the Concomitant medications/Significant non-drug therapies after start of study drug eCRF.

### 5.5.8 Prohibited treatment

Use of the treatments displayed in Table 5-1 is **not** allowed within the specified time period. No washout of these prohibited drugs will be performed during or prior to screening with the intention to make a patient eligible for study participation.

**Table 5-1 Prohibited treatment**

| Medication                                                                                                | Time window                                                               | Actions to be taken                                                                                                                                                                                    |
|-----------------------------------------------------------------------------------------------------------|---------------------------------------------------------------------------|--------------------------------------------------------------------------------------------------------------------------------------------------------------------------------------------------------|
| Any drug to treat portal hypertension (e.g. vasodilators such as non-selective beta blockers or nitrates) | Within 1 month prior to screening (visit 1) until (and including) visit 2 | - Treat as screen failure
- Don't administer study treatment / discontinue study treatment
- Record on the Concomitant medications/Significant non-drug therapies after start of study drug eCRF |
| Diuretics (incl. spironolactone)                                                                          | From screening (visit 1) to visit 2                                       | - Treat as screen failure
- Don't administer study treatment / discontinue study treatment
- Record on the Concomitant medications/Significant non-drug therapies after start of study drug eCRF |

### 5.5.9 Discontinuation of study treatment and premature patient withdrawal

Patients may voluntarily withdraw from the study for any reason at any time. They may be considered withdrawn if they state an intention to withdraw, fail to return for visits, or become lost to follow-up for any other reason.

If premature withdrawal occurs for any reason, the investigator must make every effort to determine the primary reason for a patient's premature withdrawal from the study and record this information on the Study Completion eCRF.

The investigator should discontinue the study treatment for a given patient or withdraw the patient from study if, on balance, he/she believes that continuation would be detrimental to the patient's well-being.

Study treatment must be discontinued under the following circumstances:

- Withdrawal of informed consent
- Emergence of clinically significant adverse events at the discretion of the investigator
- Any other protocol deviation that results in a significant risk to the patient's safety

Signs or symptoms of hypotension or blood pressure less than either SBP <90 and/or DBP <50 mmHg should be thoroughly evaluated by the investigator and if clinically warranted, the patient must be permanently discontinued from study drug.

Patients who discontinue study treatment should **not** be considered withdrawn from the study. A Study Drug Discontinuation form should be completed, giving the date and primary reason for stopping study treatment. See [Section 6](#) for the required assessments of these patients after discontinuation of study treatment.

For patients who are lost to follow-up (i.e. those patients whose status is unclear because they fail to appear for study visits without stating an intention to withdraw), the investigator should show "due diligence" by documenting in the source documents steps taken to contact the patient, e.g. dates of telephone calls, registered letters, etc.

Patients who are prematurely withdrawn from the study will be replaced by an equal number of newly enrolled patients only if they are discontinued prior to the completion of the second MRA data acquisition period (part A) or if final PV and IVC pressure measurements at visit 2 are not made (part B).

#### **5.5.10 Emergency unblinding of treatment assignment**

Not applicable.

#### **5.5.11 Study completion and post-study treatment**

The study is considered completed for an individual patient after the patient's visit 3 has been completed. Patients already in screening when the planned enrolment is met and the last visit 2 has been successfully completed will not be enrolled/randomized/assigned to study treatment.

No post-study treatment will be provided by Novartis.

The investigator must provide follow-up medical care for all patients who are prematurely withdrawn from the study, or must refer them for appropriate ongoing care.

No recommendations for initiating other treatment outside the study are provided.

#### **5.5.12 Early study termination**

The study can be terminated at any time for any reason by Novartis. Should this be necessary, the patient should be seen as soon as possible and treated as described in [Section 6](#) for a prematurely withdrawn patient. The investigator may be informed of additional procedures to be followed in order to ensure that adequate consideration is given to the protection of the patient's interests. The investigator will be responsible for informing IRBs and/or ECs of the early termination of the trial.

## **6 Visit schedule and assessments**

[Table 6-1](#) lists all of the assessments and indicates with an "X" the visits at which they will be performed (some of them apply only for part A or B or patients receiving serelaxin respectively).

Patients should be seen for all three visits on the designated day. However, falling outside this visit window will not constitute a protocol deviation. The investigator will bring the patient

back in for study visit as close as possible to recommended visit schedule. Documentation of attempts to contact the patient should be recorded in the patient's record.

**Table 6-1 Assessment schedule**

| Visit                                                                                                   |          | 1   | 2              |                |                |                | 3 (EOS) and SDD/PPW |
|---------------------------------------------------------------------------------------------------------|----------|-----|----------------|----------------|----------------|----------------|---------------------|
| Day*                                                                                                    | Category | -7* | 1              |                |                |                | 29*                 |
|                                                                                                         |          |     | 0min**         | 1-119min**     | 120min**       | Recovery**     |                     |
| Obtain informed consent                                                                                 | S        | X   |                |                |                |                |                     |
| Check inclusion and exclusion criteria                                                                  | S        | X   | X              |                |                |                |                     |
| Demography and medical history                                                                          | DS       | X   | X              |                |                |                |                     |
| History of portal hypertension and cirrhosis and alcohol status                                         | DS       | X   | X              |                |                |                |                     |
| Concomitant medication                                                                                  | DS       | X   | X              |                |                |                | X                   |
| Physical Exam                                                                               | S        | X   | X              |                |                |                | X                   |
| Height                                                                                                  | DS       | X   |                |                |                |                |                     |
| Weight                                                                                                  | DS       | X   |                |                |                |                |                     |
| Vital signs (incl. blood pressure measurements)                                                         | DS       | X   | X              | X  | X  | X  | X                   |
| Local ECG                                                                                               | DS       | X   |                |                |                |                |                     |
| Fluoroscopic monitoring to ensure correct position of catheter (part B only)                            | S        |     | X              |                | X              |                |                     |
| Screening log                                                                                           | DS       | X   |                |                |                |                |                     |
| Pregnancy test                                                                              | DS       | X   | X              |                |                |                | X                   |
| Blood sample collection for hematology (central laboratory)                                             | DS       | X   |                |                |                |                |                     |
| Blood sample collection for clinical chemistry (central laboratory)                                     | DS       | X   |                |                |                |                | X                   |
| Heart rate monitoring                                                                       | -        |     | X              | X              | X              | X              |                     |
| Central ECG                                                                                             | DS       |     | X  | X  | X  | X  |                     |
| Randomization via treatment allocation cards (part A only)                                              | DS       |     | X              |                |                |                |                     |
| Serum sample for immunogenicity assessments (serelaxin antibodies) by central laboratory  | DS       |     | X              |                |                |                | X                   |
| Serum sample for pharmacokinetic assessments (serelaxin levels) by central laboratory     | DS       |     | X              | X  | X              | X              | X                   |
| Peripheral blood collection for biomarker analysis by                                                   | DS       |     | X              |                | X              |                |                     |

| Visit                                                                                        |          | 1   | 2      |            |                |            | 3 (EOS) and SDD/PPW |
|----------------------------------------------------------------------------------------------|----------|-----|--------|------------|----------------|------------|---------------------|
| Day*                                                                                         | Category | -7* | 1      |            |                |            | 29*                 |
|                                                                                              |          |     | 0min** | 1-119min** | 120min**       | Recovery** |                     |
| central laboratory                                                               |          |     |        |            |                |            |                     |
| Portal vein blood collection for biomarker analysis by central laboratory (part B only)      | DS       |     | X      |            | X  |            |                     |
| Urine sample for biomarker analysis by central laboratory                        | DS       |     | X      |            | X              |            |                     |
| Study drug administration                                                                    | DS       |     |        | X          |                |            |                     |
| Magnetic resonance angiography (part A only)                                                 | DS       |     | X      |            | X              |            |                     |
| Direct portal vein pressure measurement (part B only)                           | DS       |     | X      | X          | X              |            |                     |
| Direct right atrial and inferior vena cava pressure measurements (part B only)  | DS       |     | X      |            | X              |            |                     |
| Serious adverse events                                                                       | DS       | X   | X      | X          | X              | X          | X                   |
| Adverse events                                                                               | DS       |     | X      | X          | X              | X          | X                   |
| Study Completion form                                                                        | DS       |     |        |            |                |            | X                   |

EOS = End of study

SDD/PPW = Study drug discontinuation/Premature patient withdrawal

S = assessment to be recorded on source documentation

DS = data to be recorded on source documentation and to be entered into the database

 A complete physical examination is required at visit 1 and 3 (EOS). A short physical examination is sufficient at visit 2.

 Blood pressure will be assessed approximately every 10 min until the completion of the MRA data acquisition/direct venous pressure measurement and approximately every 15 min until completion of the 60 min recovery period.

 Women of childbearing potential only. Local urine pregnancy tests will be performed. The visit 2 test is to be performed prior to randomization and study drug administration. In case of a positive urine pregnancy result a confirmatory serum pregnancy test has to be performed at the central laboratory.

 HR will be continuously monitored via ECG from the initiation of study drug administration to end of recovery.

 Printouts of central ECG recordings should be reviewed locally in a timely manner to ensure patient safety. The 1-119 min central ECG should be performed about 60 min after initiating study drug administration.

 Only in patients receiving serelaxin study drug.

 Additional blood samples may be collected for immunogenicity and accompanying serelaxin assessments as specified in [Section 6.6.2](#).

 At 60 min just prior to decreasing the serelaxin infusion rate from 80 to 30 µg/kg/day.

 The 120 min portal vein blood sample will be collected between the final (120 min) direct PV and the final IVC pressure measurement.

 Prior to initiating the serelaxin infusion (0min) and at 15, 30, 45, 60, 90, 105 and 120 min after initiating the serelaxin infusion portal vein pressure will be measured. Prior to first (0 min) and after last (120 min) portal vein pressure (PVP) measurement the right atrial pressure (RAP) and the inferior vena cava pressure (IVCP) will be measured.

\*The time windows between the visits are flexible (i.e. may be slightly shorter or longer than the suggested 6 or 28 days), but unnecessary delays should be avoided and treatment with study drug within one week after visit 1 should be targeted. Visit 1 central lab results must be received and reviewed by the sites prior to proceeding with

| Visit |          | 1   | 2      |            |          |            | 3 (EOS) and SDD/PPW |
|-------|----------|-----|--------|------------|----------|------------|---------------------|
| Day*  | Category | -7* | 1      |            |          |            | 29*                 |
|       |          |     | 0min** | 1-119min** | 120min** | Recovery** |                     |

visit 2.

\*\*The timing refers to the initiation of study drug administration (0min = prior to study drug administration). The serelaxin infusion is to be continued beyond 120min until all assessments are completed except urine sample collection for biomarker analysis. The recovery period starts after all 120 min assessments are completed / serelaxin infusion is stopped and lasts for at least 60min. Sample collection planned for the recovery time point should be performed at the end of the 60 min recovery period.

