#### **Risks associated with intravenous infusion of serelaxin**

The following adverse reactions have been reported for serelaxin in the completed clinical trials, which may represent potential safety risks for this study:

- Because serelaxin has vasodilatory properties, blood pressure decreases (defined as a SBP decrease >40 mmHg or any SBP measurements of less than 100 mmHg) were reported with serelaxin in chronic heart failure (CHF) patients. Serelaxin treatment of systemic sclerosis was also associated with decreases in blood pressure generally within normal ranges. Patients should have blood pressure monitoring while receiving serelaxin and it should not be administered to patients who are at risk of developing hypotension during vasodilator therapy.
- Increases in serum creatinine have been observed in CHF subjects receiving serelaxin but were asymptomatic.
- Menometrorrhagia, which may be associated with anaemia. Based on the pharmacology of serelaxin, menorrhagia, metrorrhagia, and dysmenorrhea are not unexpected consequences

of serelaxin administration. These events did not frequently result in discontinuation, and with lower doses and/or local administration, they may not occur.

- In CHF patients, a decrease in hemoglobin/hematocrit (up to 7%) occurred within hours of dosing but was asymptomatic.
- Antibody formation to serelaxin has occurred in 30% of subjects receiving serelaxin, but only after chronic s.c. administration. To date, the antibodies have been associated with no apparent adverse events. There is no evidence that the antibodies are neutralizing, nor is there evidence of any long-term sequelae.
- As with any protein, there is a possibility of hypersensitivity reactions, such as itching or skin rash, as well as the possibility of a potentially serious allergic reaction, which may result in hospitalization or even death. To date, no serious allergic reaction has been reported in the clinical studies.

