##### **6.5.5.1 Hematology**

Hemoglobin, hematocrit, red blood cell count, white blood cell count with differential, and platelet count will be measured.

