#### **Laboratory data**

##### **Part A (MRA)**

The summary of laboratory evaluations will be presented for two groups of laboratory tests (hematology and serum chemistry). Descriptive summary statistics for the change from baseline to each study visit will be presented. These descriptive summaries will be presented

by test group, laboratory test and treatment group. Change from baseline will only be summarized for subjects with both baseline and post baseline.

For each parameter, the maximum change from baseline within each study period will be analyzed analogously.

In addition, shift tables will be provided for all parameters to compare a subject's baseline laboratory evaluation relative to the visit's observed value. For the shift tables, the normal laboratory ranges will be used to evaluate whether a particular laboratory test value was normal, low, or high for each visit value relative to whether or not the baseline value was normal, low, or high. These summaries will be presented by laboratory test and treatment group. Shifts will be presented for most extreme values post-baseline.

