### Hematology

|                |                              |
|----------------|------------------------------|
| RBC count      | >50% increase, >20% decrease |
| Hemoglobin     | >50% increase, >20% decrease |
| Hematocrit     | >50% increase, >20% decrease |
| WBC count      | >50% increase, >50% decrease |
| Platelet count | >75% increase, >50% decrease |

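### Hematology is scheduled at screening only, so the hematology change, maximum-change and shift tables planned for both parts cannot be produced for any patient

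*Protocol*

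**What the plan says.** **Schedule.** Section 6 of the protocol says that Table 6-1 "lists all of the assessments and indicates with an" X the timing of each. The row "Blood sample collection for hematology (central laboratory" has one X, at Visit 1 (Day -7). It is blank at all four Visit 2 time points and in the last column, which covers Visit 3, study drug discontinuation and premature withdrawal. The next row, "Blood sample collection for clinical chemistry (central laboratory", is marked at Visit 1 and in that last column.

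**Tests.** Section 6.5.5.1 gives the panel without any timing: "Hemoglobin, hematocrit, red blood cell count, white blood cell count with differential, and platelet count will be measured". The sample log in Appendix 4 covers only pharmacokinetic, immunogenicity and biomarker samples.

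**Analysis.** Section 9.5.3 (Laboratory data) states, in the same words for Part A and Part B: "The summary of laboratory evaluations will be presented for two groups of laboratory tests (hematology and serum chemistry". It continues: "Descriptive summary statistics for the change from baseline to each study visit will be presented". It restricts change from baseline to patients who have both values. It then adds the maximum change in each study period for every parameter, and shift tables for all parameters.

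**Notable values.** Appendix 1 defines clinically notable results as percent changes from baseline. For red cells, haemoglobin and haematocrit the limits are ">50% increase, >20% decrease".

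**Risk.** Section 3.6 lists among the potential risks for this study: "In CHF patients, a decrease in hemoglobin/hematocrit (up to 7%) occurred within hours of dosing but was asymptomatic". Section 6.5.6 names hematology as one of the trial's safety measures.

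**The concern.** The analysis section commits the trial to comparisons that need a value after dosing, and the schedule collects none. A statistical analysis plan cannot repair this, because it can only analyse samples that were taken.

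Two things are at stake. First, the hematology part of the safety output would be empty, and an empty table can be misread as showing no effect. Second, the protocol itself names a hematological effect of serelaxin and describes it as asymptomatic, so spontaneous adverse event reporting is a poor substitute for a measurement. Safety and tolerability is a secondary objective of both parts, and Section 3.6 says that serelaxin has not been studied before in cirrhosis with portal hypertension.

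**Working it through.** No sample size, power or alpha figure is involved, and the plan gives no figure of its own to reproduce. The check counts scheduled samples and compares the count with what each planned output needs.

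**Inputs**
- Part A: 40 patients at 1:1, so 20 per arm (Section 5.2).
- Part B: 6 patients, all on serelaxin (Section 5.2).
- Total: 40 + 6 = 46. On serelaxin: 20 + 6 = 26.
- Scheduled samples per patient, from Table 6-1:

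| Test group | Before dosing | Visit 2, after dosing | Visit 3 / discontinuation / withdrawal |
|---|---|---|---|
| Hematology | 1 | 0 | 0 |
| Clinical chemistry | 1 | 0 | 1 |

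**What each output needs**
1. Change = post-baseline value − baseline value. Post-baseline hematology values per patient: 0. Evaluable patients: 46 × 0 = 0.
2. Maximum change is taken over the post-baseline changes. With none, it is undefined for all 46.
3. A shift pairs the baseline category with a post-baseline category. There are 0 pairs in 46 patients.
4. The Appendix 1 criteria use 100 × (post-baseline − baseline) / baseline. None of the five hematology criteria (red cells, haemoglobin, haematocrit, white cells, platelets) can be evaluated.

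For chemistry the same count gives up to 46 of 46 patients with a baseline and a post-dose value. The contradiction is therefore confined to hematology.

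**Would a later sample show the listed effect?** Section 3.6 places the haemoglobin/haematocrit fall in the hours after dosing. A Visit 3 sample, about 4 weeks later, would fill the tables but miss that window. The end-of-recovery draw at Visit 2 falls inside it. Using the expected maximum infusion times in Section 3.1, it comes about 180 + 60 = 240 minutes after the start in Part A and 130 + 60 = 190 minutes in Part B. A fall of 7% leaves 0.93 of baseline, and the notable limit for a decrease is 0.80 of baseline. Such a fall would appear in the mean change and perhaps in shifts, but not as a notable value.

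**Who can still be sampled?** Amendment 1 reports that Part A enrolment is complete and that 4 Part B patients have been entered. That leaves 6 − 4 = 2 Part B patients, plus any replacements and any enrolled Part A patient not yet dosed. The number of patients still awaiting Visit 3 is not given.

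**The case against.** The strongest reply is that this is one short infusion in an exploratory study. Section 6.5.6 deliberately limits safety assessment to general measures. Adverse events are collected from Visit 2 through Visit 3, blood pressure is read every 10 to 15 minutes and heart rate is monitored continuously during treatment and recovery. Laboratory abnormalities judged clinically significant count as adverse events. Patients with a variceal bleed in the month before Visit 1 are excluded. The listed fall is at most 7%, well under the 20% limit. No efficacy result depends on it.

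Much of this stands. It limits the severity, and it means that a symptomatic anaemia or an unscheduled test could still be reported. It does not remove the contradiction: Section 6.5.6 itself names hematology as a safety measure, and Section 9.5.3 plans its analysis. Loss of a table mark in PDF reading cannot be fully excluded, but it is unlikely, because the row is intact and the chemistry row beside it keeps both of its marks.

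Four stronger readings are tempting and are not supported:
- **That creatinine has the same gap.** Chemistry has a scheduled post-dose value, also at discontinuation or withdrawal, which is what Section 9.5.3 needs. Section 3.6 gives no time course for the creatinine rises; only the haemoglobin/haematocrit fall is placed in the hours after dosing.
- **That a table of notable hematology changes is promised.** Section 6.5.5 and Appendix 1 define such values and commit to no table. Appendix 1 also lists CPK, chloride and uric acid, which Section 6.5.5.2 does not measure, so it is not a reliable list of outputs.
- **That a haemoglobin fall could not be detected at all.** That is true of scheduled data only.
- **That new sampling would recover all 46 patients.** Most had already been enrolled at the amendment.

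**Conclusion.** The point holds for hematology. As scheduled, 0 of 46 patients can contribute to the hematology change, maximum-change or shift outputs in either part, and the Appendix 1 hematology criteria cannot be applied. The asymptomatic haemoglobin/haematocrit decrease named as a potential risk cannot be seen in scheduled data in any of the 26 planned serelaxin patients.

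Severity is moderate. The outputs are descriptive safety summaries; the primary endpoints, sample size and eligibility are untouched. The conclusion assumes that Table 6-1 is complete, as Section 6 says, and that its hematology row was read correctly.

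**What to change.** Reconcile Table 6-1 with Section 9.5.3.

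**Patients with visits still to come.** Add a hematology tube to the chemistry draw already made at Visit 3. For serelaxin patients, also add one to the existing Visit 2 pre-dose draw and one to the existing end-of-recovery draw. The pre-dose tube matters: without it, a same-day fall would be compared with a value from about a week earlier and could not be separated from other change over that week. The cost is a little extra blood, central laboratory fees and an edit to Table 6-1, with no new visit or venepuncture. Few patients will be reached, so these data would be listed or summarised with that limitation stated.

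**All other patients.** Remove hematology from the change, maximum-change and shift outputs. State in the study report that no post-dose hematology was scheduled and that no conclusion on hematological safety is drawn. This costs only text.
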